### Data analysis of secondary hypothesis d)

The health economic evaluation of the SPIZ program focuses on a comparison between the intervention and control groups in terms of inpatient stays and the resulting costs for the statutory health insurance AOK PLUS. The latter is the statutory health insurance fund with the most insured persons in the catchment area, thus ensuring a sufficient number of test subjects for analysis.

These are standardized over the entire observation period in terms of number of stays, average length of inpatient stays, and costs per observation year.

Further analyses relate to the comparison between the two groups in terms of selected outpatient costs, costs for medications dispensed in pharmacies, patient travel costs, care level, and number of patients in palliative care.

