Due to their complexity and in view of stringent quality assurance measures, alloHCT and CAR T-cell therapy are performed in certified treatment centers [7]. Post-treatment care is challenged by the necessity for many patients, particularly those residing in rural areas of Germany, to travel significant distances (up to 200 km) to attend regular outpatient appointments or to access the cell therapy center in the event of complications possibly resulting in significant financial and physical stress for patients and their healthcare providers [13]. Furthermore, hours spent in waiting rooms and taxis could be a source of infection in a highly susceptible population.

In a previous study conducted in Boston, Massachusetts, USA, shared post-treatment care between the cell therapy center and community-based physicians after alloHCT was found to be safe, and resulted in non-inferior early NRM and improvement of short-term quality of life (QoL) at day 100; however, no long-term QoL benefit was observed at six months [14]. In Germany, structured post-treatment care programs for patients after cellular therapy currently neither exist nor receive funding from statutory health insurance.

In preparation to design this study protocol, a structured exchange was conducted with patient advocates and cell therapy centers planning to participate in the study. This exchange revealed substantial heterogeneity in post-treatment care across centers and physicians, as well as limited collaboration between healthcare sectors, e.g., hematologists at the cell therapy center, community-based hematologists, and general practitioners.

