
Case managers and onco nurses are registered nurses who have completed a three-year professional nursing program and specialist training in oncology or an equivalent qualification. Certification in case management, or a commitment to obtain such certification, is also required for the case management role. Before assuming study-related responsibilities, staff receives project-specific training covering the study procedures, use of the SMILe App and monitoring dashboard, standardized assessments, documentation requirements, and escalation procedures. The average caseload is 25 subjects in the intervention group over the whole study period per full-time-equivalent. Staff works within multidisciplinary teams comprising case managers, onco nurses, physicians, and the project coordinator. Organizational oversight is provided by the project coordinator, while clinical supervision and clinical decision-making remains the responsibility of the hematologists at the respective center.

The effectiveness of SPIZ is currently being evaluated in a randomized controlled trial (RCT) conducted in accordance with study protocol version 5 (dated November 17, 2023): In the intervention group, patients receive the measures described above, while the control group undergoes post-treatment care according to institutional standards. During the early post-cellular therapy period (day 30 to day 100), care is particularly intensive and varies between patients depending on individual needs. After approximately day 100, the intensity of medical and nursing contacts decreases according to the individual clinical trajectory in both the intervention and control arms.

To ensure coverage of a large service area with substantial rural representation, the SPIZ program is implemented at all three cell therapy centers in the federal state of Saxony, Germany: University Hospital Dresden, University Hospital Leipzig, and Klinikum Chemnitz. Structured post-treatment care plans were implemented to standardize and coordinate patient care (supplementary Figs. 1 and 2).

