	Empowerment: ◼ Shared decision making ◼ Pathway adherence ◼ Self-assessment of health status ◼ Patients’ level of information about the course of treatment and possible treatment options	Questionnaire survey using self-developed items; Qualitative interviews with patients
c) SPIZ increases satisfaction among both patients and healthcare providers with a high level of acceptance	Patients’ perspective ◼ Satisfaction with the program and/or specific components ◼ Causes for satisfaction/dissatisfaction ◼ Suggestions for improvement of the SPIZ program	Questionnaire survey with modified PSCC (Patient Satisfaction with Cancer Care*)* [19] and self-developed items; Qualitative interviews with patients
	Healthcare providers’ perspective ◼ Satisfaction with the program and/or specific components ◼ Satisfaction with communication between different healthcare provider groups ◼ Causes of satisfaction/dissatisfaction	Qualitative interviews with healthcare providers
d) SPIZ is cost-effective from the perspective of the statutory health insurance system	◼ Rates and costs of rehospitalizations ◼ Costs of outpatient treatments and medication ◼ Travelling costs ◼ Level of care related and palliative care costs	REDCap-based project database, Statutory health insurance routine data from AOK PLUS

*alloHCT* allogeneic hematopoietic cell transplantation, *CAR* T-cell therapy, chimeric antigen receptor T-cell therapy, *GvHD* graft-versus-host disease, *QoL* Quality of Life, *REDCap* Research Electronic Data Capture, *SMILe* SteM-cell-transplantatIon faciLitated by eHealth, *SPIZ* cross-sector care for patients with hematological diseases following innovative cell therapy

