Overall, the present study addresses the substantial need for intensive and structured post-treatment care following cellular therapy, particularly in rural regions, by implementing an interdisciplinary, digitally supported, cross-regional and cross-sectoral care model. Owing to the specific funding structure, a positive evaluation would enable long-term reimbursement of the SPIZ program for all patients insured under the statutory health insurance system in Germany, thereby improving care sustainably for this vulnerable patient population.

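### Secondary hypothesis d) asserts cost-effectiveness, but the outcomes and analysis stated for it include neither the program's own cost nor any relation of cost to effect

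*Protocol article*

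**What the plan says.** Table 1 (Hypotheses and outcomes) gives hypothesis d) as "SPIZ is cost-effective from the perspective of the statutory health insurance system". Its outcomes begin with "Rates and costs of rehospitalizations" and continue with outpatient and medication costs, travel costs, and costs linked to care level and palliative care. The data sources are the REDCap project database and AOK PLUS routine data.

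The section Data analysis of secondary hypothesis d) says that the evaluation "focuses on a comparison between the intervention and control groups in terms of inpatient stays and the resulting costs for the statutory health insurance"; the fund in question is AOK PLUS. The measures are "number of stays, average length of inpatient stays, and costs per observation year". Further comparisons concern "selected outpatient costs, costs for medications dispensed in pharmacies, patient travel costs, care level, and number of patients in palliative care".

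Other parts of the article bear on this:
- The Introduction says that structured programs of this kind "currently neither exist nor receive funding from statutory health insurance" in Germany.
- Methods states the staffing: "The average caseload is 25 subjects in the intervention group over the whole study period per full-time-equivalent".
- The Discussion says that "a positive evaluation would enable long-term reimbursement of the SPIZ program" for patients under statutory insurance.

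**The concern.** Cost-effectiveness for a payer is a statement about the extra cost of an intervention, its own cost included, set against the extra effect. The stated analysis has neither part. It compares selected costs that arise downstream of the program.

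The omission works in one direction. Case managers and onco nurses are described under Fig. 1 as extra personnel, and Data collection and management reserves the SPIZ components for the intervention group. Enrollment, randomization and patient pathway adds that a scheduled home visit with its video consultation takes the place of a routine clinic visit. A clinic visit or journey avoided in this way can therefore count as a saving under the listed items, while the service that replaced it is listed nowhere as a cost.

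At stake is the reading of hypothesis d). A statutory insurer could take a fall in downstream cost as evidence of cost-effectiveness without seeing what it would have to pay to obtain that fall.

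**Working it through.** **1. Hypothesis and analysis side by side.** The article gives no cost, ratio or threshold, so there is no planned figure to reproduce.

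| Element | Table 1, d) | Analysis section, d) |
|---|---|---|
| Inpatient | rates and costs of rehospitalization | stays, length of stay, costs per observation year |
| Outpatient, medication, travel | costs | costs (outpatient: selected) |
| Care level, palliative care | costs | care level; number of palliative patients |
| Case managers, onco nurses, home visits | not named | not named |
| Video consultations, case conferences, app | not named | not named |
| Cost related to effect (ratio, net benefit, cost per event avoided) | not named | not named |

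The rest of the article contains no program costing and no measure joining cost to effect.

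**2. What the comparison can show.** Let D be the downstream cost per patient in the control arm minus that in the SPIZ arm, and let P be the program cost per SPIZ patient. The plan as written reports D. The payer's net saving under reimbursement would be D − P. Whenever 0 < D < P, the comparison shows a saving although the payer would face a net extra cost. That extra cost might still be worth the clinical gain, but this is the question cost-effectiveness asks, and no stated analysis addresses it.

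**3. Size of P in staff.** Inputs are 153 patients per group (Results) and 25 patients per FTE (Methods). I read the caseload as pooling both nursing roles, which gives the smaller number.

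153 / 25 = 6.12 FTE

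This is the only size that follows from the article.

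**4. Illustration in money.** Salary and duration are assumptions, not figures from the article. If the 6.12 FTE are employed for the whole of 2 to 3 years:

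- Low: 6.12 × 60,000 × 2 = 734,400 EUR; / 153 = 4,800 EUR per patient
- High: 6.12 × 80,000 × 3 = 1,468,800 EUR; / 153 = 9,600 EUR per patient

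With 50,000 EUR per FTE-year and 2 years, the low end is 6.12 × 50,000 × 2 / 153 = 4,000 EUR.

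The caseload wording can also be read as 25 patients at a time. With the planned 12 to 24 months of treatment per patient, the range would then be 60,000 × 1/25 = 2,400 EUR to 80,000 × 2/25 = 6,400 EUR.

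**5. Set against the planned effect.** Sample size assumes a fall from 55% to 35%, a difference of 0.20. On the range 4,800 to 9,600 EUR, staff cost per additional event-free patient is 4,800 / 0.20 = 24,000 EUR to 9,600 / 0.20 = 48,000 EUR, before any downstream saving. App, video platform, travel and physician time are not included.

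**The case against.** The strongest reply is that this is a short article section, while a full protocol and SAP exist and are not shown. Costing methods usually sit there. The wording is open (a focus, further analyses, a selection of outpatient costs), and nowhere does the article say that program cost is excluded. REDCap is also a named source for d) and holds process data, so the means to cost the program may already be assigned to this hypothesis.

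This limits the point to what the article states. It does not remove it: the article fixes the hypothesis, lists its outcomes and describes its analysis, and these do not match. The contacts are counted as fidelity measures, and nothing says that they will be costed.

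Four stronger readings are tempting and should not be made:
- *That program cost is certain to be missing from the claims.* The Introduction describes current funding and the Discussion mentions a special funding structure. The supportable statement is that AOK PLUS routine data would not be expected to carry this cost.
- *That costs per observation year give extreme values for patients who die early.* This happens only if each patient's cost is divided by that patient's own time and then averaged. Total group cost over total group time fits the text equally well.
- *That 12-month costs need weighting for censoring.* Follow-up is at least 12 months, expected drop-out is 5%, and death does not censor cost.
- *That reimbursement turns on d).* The Discussion ties it to a positive evaluation in general, and the confirmatory test is of the clinical endpoint.

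**Conclusion.** The point holds as a mismatch between a stated hypothesis and its stated analysis. Followed as written, the plan yields a comparison of selected downstream insurer costs that leaves out a cost borne only in the SPIZ arm, and it cannot establish that SPIZ is cost-effective.

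The omitted staffing is about 6.1 FTE for 153 patients. The euro ranges show that the omission is unlikely to be negligible, but they rest on assumed salaries and durations and on how the caseload is read. The conclusion does not depend on them: it needs only P > 0 and the absence of a cost-effect measure.

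The article does not show that the sponsor has decided to exclude program cost, and the full plan may include it. Hypothesis d) is secondary with no confirmatory test described, so this should be corrected but does not threaten the primary analysis.

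**What to change.** In Table 1 and in the analysis section for d):
1. Add program cost per intervention patient to the SPIZ arm: the recorded case management contacts, home visits, video consultations and case conferences times unit costs, plus app cost.
2. Report incremental cost together with the effect difference and an uncertainty interval, for example as cost per primary event avoided or as net benefit. The choice is the sponsor's, but it should be fixed before the data are analysed. Because claims exist only for AOK PLUS members, cost and effect should come from the same patients, or the difference in populations should be stated.
3. If program cost cannot be added, rename d) as a comparison of statutory insurance expenditure excluding program cost, and draw no conclusion of cost-effectiveness.

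If the full protocol or SAP already does this, a sentence in the article is enough.

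The cost is modest. The counts are already collected as fidelity data; unit costs and app cost have to be assembled. First results are expected in mid-2027 and amendments can be registered, so there is time. The downside is a less favourable cost figure for SPIZ. No trial procedure changes.

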### Hypotheses and outcomes

The primary hypothesis is that patients receiving the SPIZ intervention following cellular therapy (intervention group) experience better health outcomes in terms of lower mortality and fewer hospital readmissions than patients receiving routine clinical care (control group). The target population comprises all adult patients with hematologic diseases who undergo alloHCT or CAR T-cell therapy at one of the three participating centers.

Efficacy will be evaluated using a composite primary endpoint comprising mortality and disease-related rehospitalization. The latter is defined as unplanned rehospitalization due to complications typically associated with either the underlying hematologic disease (e.g., disease progression) or cellular therapy. Such complications include infections and organ toxicities following either therapy, GvHD following alloHCT, and CRS or neurotoxicity, such ICANS, following CAR T-cell therapy. The primary endpoint will be evaluated by confirmatory statistical analysis 12 months after cellular therapy.

Secondary hypotheses with corresponding outcomes and data sources are listed and described in Table 1.

**Table 1 Tab1:** Overview of the secondary hypotheses. The four secondary hypotheses to be examined are listed along with their corresponding secondary outcomes and the respective data sources or scales

Secondary hypotheses	Secondary outcomes	Data source / scale
a) SPIZ leads to improved longitudinal clinical outcomes	◼ Mortality ◼ Complications, e.g., infections, GvHD (alloHCT), CRS (CAR T-cell therapy), neurotoxicity (CAR T-cell therapy), relapse, and death assessed by incidence and duration (as feasible) ◼ Rates and duration of unplanned rehospitalizations ◼ Symptom burden, including nutrition, body weight, body temperature, skin changes, bowel habits, and neurological symptoms ◼ Laboratory values ◼ Therapy adjustments ◼ Conducted assessments, e.g. staging, pulmonary function testing, echocardiography	REDCap-based project database, SMILe system
b) SPIZ leads to improvements in QoL and patient empowerment	QoL assessed using established questionnaires	EORTC QLG Core Questionnaire QLQ-C30 and module for low-grade non-Hodgkin lymphoma QLQ-NHL-LG20 [17], NCCN Distress-Thermometer (German version) [18]

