### Data analysis regarding primary hypothesis and secondary hypothesis a)

The confirmatory test of the primary outcome at 12 months will be performed using Fisher’s exact test. All outcomes of secondary hypothesis a) are presented descriptively for the intervention and control groups according to the respective survey dates. The same applies to the primary combined outcome at time points 6, 18, and 24 months. Metric values will be compared between groups in terms of their means or, in the case of skewed distributions, their medians; categorical values will be compared in terms of their distributions. For events (death/ complication/ hospitalisation), survival time analyses and hazard ratios will be calculated. Logistic or Poisson regressions will be used to estimate effect size measures (odds ratios or relative risks). In addition, the control and intervention groups will be compared with regard to potential confounders. Should serious biases occur despite randomization, these will be addressed as appropriate through adjustments, subgroup analyses, or sensitivity analyses.

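### Average length of stay and event duration exist only for patients with the event, so comparing them between arms is not a randomized comparison; add inpatient days per randomized patient

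*Protocol article*

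**What the plan says.** The section on data analysis of secondary hypothesis d) compares the arms on inpatient stays and the resulting costs to AOK PLUS. Of these quantities it says: "These are standardized over the entire observation period", in terms of "number of stays, average length of inpatient stays, and costs per observation year".

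Table 1, under secondary hypothesis a), lists "Rates and duration of unplanned rehospitalizations" and has complications "assessed by incidence and duration (as feasible").

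The analysis section for the primary hypothesis and hypothesis a) adds three relevant statements:

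- "Metric values will be compared between groups in terms of their means or, in the case of skewed distributions, their medians"
- "All outcomes of secondary hypothesis a) are presented descriptively for the intervention and control groups"
- "For events (death/ complication/ hospitalisation), survival time analyses and hazard ratios will be calculated"

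The section on principles of the analyses puts all analyses in the intention-to-treat population and drops individuals with a missing value from the sub-analysis concerned. The article does not say that a patient without a stay or complication counts as zero days. It names no total of inpatient days per randomized patient.

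**The concern.** The denominator of an average length of stay is the number of stays. The duration of a rehospitalization or complication, read naturally, exists only in a patient who had one. Whether a patient belongs to that group is decided after randomization, and the trial's purpose is to change it. Once SPIZ changes who is admitted, the admitted patients in the two arms need no longer be alike, and a difference in average stay mixes a treatment effect with a change in case mix.

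The intention-to-treat statement does not cure this, because it cannot give a length of stay to a patient who was never admitted. The rule of excluding missing values, if anything, favours the event-only reading. Means, medians and per-year standardization leave the conditioning in place. Durations can also be cut short by death, so an early death can look like a short complication.

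At stake is how hypotheses a) and d) are read: a longer average stay under SPIZ could be taken as an unfavourable effect when it only reflects that the shorter admissions were prevented.

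**Working it through.** The article gives no figure for length of stay or complication duration, so there is no stated result to reproduce. The check is whether the average can move against the total, and when.

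**Inputs from the article.** Control rate 55% and target rate 35% (sample size section); 153 patients per group (Results). The 55% is a rehospitalization rate after alloHCT, and the 35% refers to mortality or disease-specific rehospitalization. Treating both as the share of patients with a stay is a simplification.

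**Assumptions not in the article.** One stay per hospitalized patient; the split into short and long stays; their lengths; and the remaining stays keep their length.

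**Who contributes.** 153 × 0.55 ≈ 84 control patients and 153 × 0.35 ≈ 54 SPIZ patients would have a length of stay. Fewer would in the insurer data, which cover AOK PLUS members only.

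**Condition for a reversal.** Let the control arm have *n* stays and *T* days, and let SPIZ avert *a* stays totalling *d* days. The total falls to *T* − *d*. The average becomes (*T* − *d*)/(*n* − *a*), which exceeds *T*/*n* exactly when *d*/*a* < *T*/*n*: the averted stays are shorter than the control average.

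**Only short stays averted, per 100 patients.**

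- Control, 25 stays of 20 days and 30 of 6 days: 25×20 + 30×6 = 680 days; 680/55 = 12.4 days per stay.
- SPIZ, 20 short stays averted: 25×20 + 10×6 = 560 days; 560/35 = 16.0 days per stay.
- Total: 560/680 − 1 = −18%. Average: 16.0/12.36 − 1 = +29%.

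Two other mixes, again with 20 short stays averted:

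| Control mix | Average per stay | Total days |
|---|---|---|
| 25 stays of 14 days, 30 of 7 days | 560/55 = 10.2 to 420/35 = 12.0 (+18%) | 560 to 420 (−25%) |
| 15 stays of 20 days, 40 of 5 days | 500/55 = 9.1 to 400/35 = 11.4 (+26%) | 500 to 400 (−20%) |

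**Other patterns of averted stays.** Here short stays last 4 days and long stays 20 days. Control has 30% short and 25% long: 0.30×4 + 0.25×20 = 6.2 days per randomized patient, and 6.2/0.55 = 11.3 days per stay.

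| SPIZ arm | Days per stay | Days per randomized patient | Reversal |
|---|---|---|---|
| 13% short, 22% long (mostly short averted) | 4.92/0.35 = 14.1 | 4.9 | yes |
| Short and long averted in proportion | 3.95/0.35 = 11.3 | 3.9 | no |
| 30% short, 5% long (only long averted) | 2.2/0.35 = 6.3 | 2.2 | no |

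For the first row, short stays of 2, 4 or 6 days were crossed with long stays of 12, 20 or 30 days. All nine combinations reverse: days per stay rise by 1.0 to 4.9, while days per randomized patient fall by 0.7 to 1.9.

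**The case against.** The best answer is that these measures do not stand alone. Number of stays and costs appear in the same sentence, Table 1 pairs each duration with incidence or rates, and survival analyses with hazard ratios are planned for events. In the example, 55 stays averaging 12.4 days and 35 averaging 16.0 days multiply back to 680 and 560 days, so a reader with both figures can recover the totals. This stands and limits the harm. It does not remove the problem: the article plans no total as a between-arm measure with its own estimate and interval, and a longer average beside a lower count does not show whether the longer stay is an effect or selection.

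Second, the wording is loose. Standardization per observation year could be meant to yield inpatient days per year, duration is undefined and subject to feasibility, and zeros may be set in the statistical analysis plan, which is not shown. This also stands. The absence of a zero rule from an article is no fault in itself; the point is the stated choice of average stay, and of duration on its natural reading, as measures compared between arms.

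Third, hypothesis a) is descriptive, mortality is reported as an outcome in its own right, and the confirmatory test concerns the binary composite. All correct.

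A reader might go further and infer that the trial judges hospital burden by these measures alone, or that it will report the wrong direction. The documents support neither: the companion measures are named, and a reversal needs averted stays shorter than the control average, on which the article gives no data.

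**Conclusion.** The point holds in a limited form. Average length of stay and, on its natural reading, duration of rehospitalizations and complications are conditional on the event, and their contrast between arms is not protected by randomization. If SPIZ averts mainly short stays, the average can rise by 18% to 29% while total days fall by 18% to 25%, over the three mixes in which only short stays are averted. Under proportional prevention or prevention of long stays alone, the direction does not reverse. The lengths, the severity split and one stay per patient are assumptions; only the 55%, the 35% and the group size come from the article.

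The consequence is confined to the interpretation of secondary hypotheses a) and d); the primary test is untouched. It might seem to follow that average length of stay should be removed. It need not be: it is a legitimate description of the patients who were admitted, provided it is not presented as a treatment effect.

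**What to change.** Before the analysis, make these changes:

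1. Add, as the between-arm measure of hospital burden, total unplanned inpatient days per randomized patient over 12 months, counting 0 for patients without a stay. For insurer data, use all randomized AOK PLUS members.
2. Because early death also lowers inpatient days, report this total beside mortality, or as days alive and out of hospital. The Results section says patients were usually randomized several days before the expected discharge, so the count must exclude remaining days of the index stay.
3. Keep mean length per stay and event duration as description among patients with the event, labelled as not a treatment comparison.
4. Report complication days per randomized patient only where start and end dates are recorded. The article does not describe such dates, and its feasibility qualifier suggests they may be incomplete.

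The cost is slightly more analysis work and an outcome with many zeros and a long tail, hence wider intervals. The inpatient total needs admission and discharge dates or lengths of stay, which the planned length-of-stay analysis already implies, though the article does not list them. Enrolment ended in January 2026 and first results are expected in mid-2027, so this can be settled in time.
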